## CALCULATION OF THE SIZE OF STUDY

In this trial, the patients were randomized into 2 groups:

- Group 1: group educational intervention by peer educators associated with classical management
- Group 2: classical management without peer education

This is a randomized trial comparing open impact on HbA1c of a 1 year peer education compared to a conventional monitoring alone in health centre.

The comparison group is on HbA1c, the primary judgement criteria. The test is a test of superiority. It is assumed that in the reference group, the value of HbA1c is 8.5% and with a **standard deviation of 2.0**, (previous study conducted in the framework of the NGO Santé Diabète Mali under publication) and we consider that the strategy would be interesting if the assessed value of the mean HbA1c decreased by 1 percentage point of HbA1c and the standard deviation of 0.5 .

In this situation, with a risk  $\alpha$  of 5% and a power  $1-\beta$  of 80%, we must include 60 patients in each group.

in order to take into account a proportion up to 20% of patients lost of sight, we decided to recruit 75 patients per group that is to say 150 patients in total.

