## STATISTICAL METHODS USED

The data will be analyzed by a medical epidemiologist with the Epi Info software.

Initially, we will proceed to the description of the included patients and compare the characteristics of both groups of patients to detect any differences at inclusion. These characteristics are expressed as percentage for qualitative variables and as mean and median and their dispersions parameters, respectively, standard deviation and interquartile 25 and 75. The comparison of characteristics between the two groups will be performed using appropriate tests, the exact X2 or Student's t-test. Then, a uni-variable analysis of variance analysis type will be conducted to identify variables to include in the multivariable explanatory models. The inclusion threshold chosen will be 0.25. Data will be expressed as means  $\pm$  SD unless indicated otherwise. Comparisons within groups were performed using analysis of variance by comparing the averages using the comparison test of averages or the Student's t-test.

The comparison between groups will be conducted by analysis of variance, using the Bonferroni correction where appropriate. The results will be statistically significant at  $p < 0.05$ .

**Direct beneficiaries in Mali:** The 150 diabetic patients directly reached by the activities / The 15 peer educators trained in the action areas selected in Mali. The 25 health agents of the action areas selected in Mali / Families and relatives of patients reached by animations (10 000 persons)

**Indirect beneficiaries in Mali :** All the diabetic patients of Mali (3% of the adult population) / All the health workers involved in the management of diabetes in Mali / The Malian health systems / The Malian population by reducing the risk factors of diabetes and increasing the quality of life

**Indirect beneficiaries in Africa:** Diabetic patients of French and English speaking African countries which will benefit from the methodology and tools developed

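### The between-group analysis of variance assumes equal variances, although the sample-size section plans on different SDs; a minor robustness gap if completer numbers also differ between arms

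*Supplement*

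**What the plan says.** Statistical methods used, on the outcome comparison: "The comparison between groups will be conducted by analysis of variance", with a Bonferroni correction where it applies. The significance threshold is p < 0.05. No Welch version, variance check or robust standard error appears.

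Student's t-test is named in the same section for two other purposes:
- differences at inclusion: "The comparison of characteristics between the two groups will be performed using appropriate tests, the exact X2 or Student's t-test";
- within-group comparisons: "Comparisons within groups were performed using analysis of variance by comparing the averages using the comparison test of averages or the Student's t-test".

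Calculation of the size of study, on the spread of HbA1c: "It is assumed that in the reference group, the value of HbA1c is 8.5% and with a" "standard deviation of 2.0". The strategy is judged worthwhile if the mean "decreased by 1 percentage point of HbA1c and the standard deviation of 0.5". The section arrives at 60 patients per group for 80% power at α = 5%, then recruits 75 per group "in order to take into account a proportion up to 20% of patients lost of sight". Loss is not split by arm.

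Main judgment criteria defines the primary endpoint as the change in HbA1c from inclusion to one year. The size section describes the trial as open.

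**The concern.** With two groups, classical analysis of variance is the pooled-variance t-test (F = t²). It estimates one common variance and uses it for both arms. The design section expects the arms to differ in spread, so the two sections do not share the same assumption.

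Unequal variances do little harm when the analysed arms are about the same size. Recruitment is equal at 75 and 75, but the analysis depends on completers. The trial is open and only one arm attends peer sessions, so unequal retention is plausible, although the documents do not say which arm would lose more. If the more variable arm ends up smaller, the pooled standard error is too small, intervals are too narrow and the test rejects too often. If it ends up larger, the reverse happens.

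**Working it through.** **Inputs.** From Calculation of the size of study: SD 2.0 in the reference group; 0.5 read either as the intervention SD or as a fall to 1.5; difference 1 point; α 5% (taken as two-sided, since sidedness is not stated); power 80%; 75 recruited per group; loss up to 20%. How loss splits by arm is my assumption: 20% in one arm and none in the other leaves 60 and 75 completers.

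**The plan's own figure first.** n per group = (s₁² + s₂²)(1.960 + 0.842)² / 1², where (1.960 + 0.842)² ≈ 7.849.

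| SDs (reference / intervention) | s₁² + s₂² | n per group |
|---|---|---|
| 2.0 / 2.0 | 8.00 | 62.8 → 63 |
| 2.0 / 1.5 | 6.25 | 49.1 → 50 |
| 2.0 / 0.5 | 4.25 | 33.4 → 34 |

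None gives 60. A common SD of 2.0 comes nearest: 60 per group then has 78.2% power. The dropout step does reproduce: 60 / (1 − 0.20) = 75.

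**Pooled against true standard error.** With n_C control and n_I intervention completers:
- pooled variance s_p² = [(n_C − 1)s_C² + (n_I − 1)s_I²] / (n_C + n_I − 2);
- variance the test uses = s_p²(1/n_C + 1/n_I);
- true variance of the mean difference = s_C²/n_C + s_I²/n_I;
- large-sample error = 2Φ(−1.96 × √(used / true)).

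*SDs 2.0/0.5, completers 60/75 (control/intervention).* s_p² = (59 × 4 + 74 × 0.25)/133 = 254.5/133 = 1.9135. Used: 1.9135 × 0.03 = 0.0574. True: 4/60 + 0.25/75 = 0.0700. √(0.0574/0.0700) = 0.906, so the pooled standard error is about 9% too small. Error: 2Φ(−1.775) = 7.6%.

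*SDs 2.0/0.5, completers 75/60.* s_p² = (74 × 4 + 59 × 0.25)/133 = 310.75/133 = 2.3365. Used: 0.0701. True: 4/75 + 0.25/60 = 0.0575. Root ratio 1.104, about 10% too large. Error: 2Φ(−2.164) = 3.1%.

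**Simulation** (normal data, equal means, two-sided 5%, at least 400,000 draws per cell; separate runs agree to about 0.1 percentage point):

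| SDs | Completers (control/intervention) | Pooled test |
|---|---|---|
| 2.0/0.5 | 60/60 | 5.2% |
| 2.0/0.5 | 59/61 | 5.6% |
| 2.0/0.5 | 61/59 | 4.8% |
| 2.0/0.5 | 60/75 | 7.8% |
| 2.0/0.5 | 75/60 | 3.2% |
| 2.0/1.5 | 60/75 | 5.8% |
| 2.0/1.5 | 75/60 | 4.3% |
| 2.0/2.0 | 60/75 and 75/60 | 5.0% |

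Welch's test stays at 5.0 to 5.1% in these cells.

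**Intervals.** A shift in the mean does not alter the error of estimation or its standard error, so coverage of the nominal 95% interval is 100% minus the error above, whatever the true difference. For SDs 2.0/0.5 that is about 92% at 60/75 and 97% at 75/60.

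**Price of the alternative.** At 60 per group, SDs 2.0/0.5 and a 1-point difference, power is 96.1% pooled and 95.9% with Welch's test.

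**The case against.** The strongest reply is that the error rates describe a null that the plan never states. The 0.5 belongs to the scenario in which the intervention works. If it does nothing at all, both randomised arms share one distribution, and with non-informative loss the pooled test keeps its 5%. This stands: the test is distorted only if the means are equal while the spreads differ. It does not rescue the interval, which is miscalibrated whatever the effect once spreads and completer numbers both differ.

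Four further limits also stand.
- The 0.5 is ambiguous. Read as a fall to 1.5, the distortion is under one percentage point either way. The stated 60 per group sits closest to a common SD of 2.0, which would remove the problem, although the text does not state a common SD.
- The SDs are for the HbA1c value. The plan gives none for the change, so the ratio is carried over to the primary endpoint by assumption.
- No document says which arm would lose more, so no direction is predicted.
- Where the intervention arm loses more, the pooled test is conservative, but under SDs 2.0/0.5 the power cost is small: 97.6% pooled against 98.5% with Welch's test at 75/60, both well above the planned 80%.

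A reader might infer that any imbalance in dropout breaks the 5% level. It does not: 59/61 and 61/59 give 5.6% and 4.8%. Figures such as 9.4% or 2.4% need splits of 50/70 or 70/50, where one arm has lost 25 of 75 (33%), beyond the plan's 20%. A reader might also infer that Student's t-test is planned for the outcome comparison. It is named only for baseline and within-group comparisons, so the point rests on the analysis of variance.

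**Conclusion.** The point holds as a minor robustness gap. The analysis section assumes equal variances, the design section plans on unequal ones under either reading of the 0.5, and nothing else in the protocol reconciles them.

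The size is conditional on unequal spread together with the most uneven split within the plan's allowance (20% loss in one arm, none in the other). In that case the 5% error becomes about 7.8% or 3.2% under SDs 2.0/0.5, about 5.8% or 4.3% under 2.0/1.5, and is unchanged under equal SDs. These figures assume normal data, non-informative loss, and that the SDs given for the HbA1c value also describe the analysed quantity. The documents do not support saying that the trial's type I error will be inflated. They support saying that the planned standard error is not protected if spreads and completer numbers both differ.

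**What to change.** 1. In Calculation of the size of study, state whether 0.5 is the SD in the intervention group or the amount by which the SD falls, and whether it refers to the HbA1c value or to its change.
2. In Statistical methods used, specify Welch's test for the between-group HbA1c comparison, or heteroscedasticity-robust standard errors if a regression or ANCOVA is fitted. Confirm that the named software can produce it.

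Welch's test is valid under every reading of the 0.5, so the second change need not wait for the first. For the other continuous outcomes the plan gives no SDs, so using the same method there would be a precaution only.

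The cost is one sentence of analysis wording plus the clarification. No extra patients are needed, and the power loss is 0.2 percentage points (96.1% to 95.9%) at 60 per group with SDs 2.0/0.5.

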## Chronogram

|                            | Month 1 - 5 | Month 6       | Month 7                  | Month 8          | Month 9      | Month 10      | Month 11       | Month 12 |
|----------------------------|-------------|---------------|--------------------------|------------------|--------------|---------------|----------------|----------|
|                            | Preparation | Randomization | Pre inclusion
T-X (*) | Inclusion
T 0 | Visit
T 3 | Visite
T 6 | Visite
T 12 |          |
| Identification of patients | ✓           | ✓             |                          |                  |              |               |                |          |
| Patient Education experts  | ✓           |               |                          |                  |              |               |                |          |
| Informed Consent           |             |               | ✓                        |                  |              |               |                |          |
| Clinical examination       |             |               | ✓                        | ✓                | ✓            | ✓             | ✓              |          |
| Laboratory tests           |             |               | ✓                        | ✓                | ✓            | ✓             | ✓              |          |
| Knowledge                  |             |               | ✓                        | ✓                | ✓            | ✓             | ✓              |          |
| Data Processing            |             |               |                          |                  |              |               |                | ✓        |
| Report                     |             |               |                          |                  |              |               |                | ✓        |

## 5. Risk management procedures

### Study of the social risks and benefits

This study will enroll human subjects in a controlled experiment that seeks to substantially alter the knowledge, feelings, behavior and health of persons who are assigned to active treatment. For all subjects, the study will collect and store sensitive personal information and expose every subject to the risks and discomfort of blood tests.

### Ethical consideration

The main ethical considerations in this study are the lack of access to peer education, randomly, of 50% of subjects of the study. While we hope that exposure to peer education is beneficial, we remain cautious about the concrete results of this action for diabetic people because such a program has never been tested before. If the evaluation of this study is conclusive, this methodology could significantly improve and prolong the lives of hundreds of thousands of diabetic people in Africa. Therefore, we believe it is ethical to refuse access to the program to half of the subjects in order to determine its value in sight to spread it to hundreds of thousands of diabetic people in Africa.

## 6. Potential risks to participants and co

### Risk minimization

The risk of breach of confidentiality and the risks linked to biological tests are minimal, as long as measures are taken to maintain data security and avoid the risk of infections and pain during samplings. To ensure confidentiality, all the study data will be stored separately and the files will be protected by password.

Only people with an obvious need for data access, such as PI, will have the passwords. To strengthen protection measures, data forms will be stored in protected cabinets. It will be important to encode these forms in order to avoid displaying data such as names, addresses, phone numbers and other personal identification data. Only the principal researcher, the co-researchers and the analysts will have access to keys linking the study identifiers to respondents' personal data. The survey forms will be kept for 5 years after the conclusion of the project to enable data validation, and then destroyed.

To minimize the risks associated with the samplings, only new and sterile equipment with disposable needles will be used.

To minimize the risks directly associated with the intervention of peer education, subjects must be fully informed about all aspects of the intervention. This information will be done through an informed consent form. All subjects will be required to sign this declaration of consent as a condition of participation in the study. In order not to exclude the illiterate people, the consent document will be read aloud to all subjects and translated by a translator for people who do not speak French. Subjects will be encouraged to ask questions and will sign the consent only after they have asked all the questions they have.

The participation of subjects will be entirely voluntary. The right of access to medical care will not be affected by the participation or not to this study.

Topics will be able to withdraw at any time.

Before starting the study, the team will have the full receipt of the ethics committee of the Faculty of Medicine, Pharmacy and Dental Medicine in Mali (FMPOS). This receipt will ensure that all commitments will be reviewed, approved and monitored by a national ethics committee. The recruitment of subjects will not begin before the reception of this receipt.

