**Method (s) :**

This study will be conducted by a multidisciplinary team that brings together high level skills in research projects and in peer education projects. It will be conducted in one site in one country Mali. This site was chosen because they meet a functional care, access to medicines and a dynamic association of diabetic patients. Peer educators and persons targeted by the project will be recruited through the local association of patients. This association will be a social support that provides on going prevention counseling, education and support services to people who have diabetes. It represents an important link between patients, educators and general medical services. The procedure will start by the training of peer educators who were identified and recruited to facilitate the sessions. Then, the 4 educational sessions: control of cardiovascular risk (blood pressure, waist circumference, smoking, cholesterol, glycaemia), control of Food (balance, fat, carbohydrates), physical activity management, insulin management, will be carried out and patients will be able to:

- Analyze knowledge that appears in various forms, including forms adapted to illiterate patients (colour codes, presence of photos)
- Act on knowledge: the patient observes, makes hypothesis, he experiments, compares, deduces, analyzes, makes relations.
- Work in interaction with other learners, which gives education a social dimension.
- Decide on the implementation of actions taking into account individual, cultural, social, economic context

For each situation, a day of training will be conducted by trained peer educators with theoretical contributions on the issue, practical scenarios, analyzes of the issues out of frame and put in "educational security ". These training days will be implemented with 8-10 patients (1Hour and an half) and the 4 sessions will take place over a period of two months starting from the inclusion of patients.

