2 groups of 75 persons will be formed. One group will have specific education using methodology of learning nests. The other group will be a control group not subject to this specific education. To evaluate, we propose a classical randomized controlled experimental (RCT) design, with randomization at the person-level. For outcome measures, we propose change in HbA1c, increase of social and emotional support and increase of linkage to clinical care. In addition to HbA1c, we propose measuring changes in systolic, diastolic blood pressure, and weight.

**Public health significance :** It is very important to find an education methodology adapted to the African context. This line of diabetes management is essential to improve the management of African diabetic patients.

**Sustainability plan:** If the evaluation of this methodology is conclusive, the Malian state will implement the methodology in the 22 diabetes units of the country.

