### **Inclusion criteria**

- Patients followed in the diabetes units of the project area and doing regular consultations
- Patients with type 2 diabetes or treated or not with insulin
- Poorly controlled diabetes with HbA1c  $\geq 8\%$
- Patients who accepted to undergo the whole process of peer education
- Patients who agreed to perform all biological measures included in the protocol
- Patients aged from 30 to 70 years old

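### The protocol plans no recording of hypoglycaemia, admissions, deaths or other adverse events in either arm, so an HbA1c result could not be read beside harm data

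*Supplement*

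**What the plan says.** Under Risk minimization the protocol says that "The risk of breach of confidentiality and the risks linked to biological tests are minimal", provided that data security and sampling hygiene are respected. The same section acknowledges that peer education carries risks of its own and answers them by informing participants and obtaining consent. It provides no monitoring or recording.

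The outcomes are spread over several sections. Taken together (the research question and methods of the scientific abstract, Secondary objectives, Main judgment criteria, Secondary judgment criteria) they are HbA1c, fasting glucose, blood pressure, weight, BMI, waist, and, in the abstract only, social support and linkage to care. The statistical methods section has no safety analysis. The chronogram shows clinical examination, laboratory tests and a knowledge assessment at T0, T3, T6 and T12, and no row for events.

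On who is treated and how, the Inclusion criteria admit "Patients with type 2 diabetes or treated or not with insulin". Main judgment criteria says that peer education aims to change diet, exercise, glucose self-monitoring and the way medicines are used. The abstract lists among the session topics "physical activity management, insulin management, will be carried out". The sample size section takes as worthwhile a result in which "the mean HbA1c decreased by 1 percentage point of HbA1c and the standard deviation of 0.5" are observed. On the use of the result, the abstract says that if it is conclusive "the Malian state will implement the methodology in the 22 diabetes units of the country".

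**The concern.** The trial intends to change how patients eat, exercise and use their medicines, some of them while on insulin. Hypoglycaemia is an obvious possible cost of lower glucose in such patients. HbA1c reflects average glycaemia and cannot show whether a fall came with low-glucose episodes. If nobody asks, the trial can report benefit and say nothing about cost, and a national decision is tied to the result.

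This cannot be left to an analysis plan. What is asked at visits is fixed by the protocol and its forms, and mild episodes that were not asked about cannot be reliably reconstructed afterwards. A further consequence is that up to 20% loss to follow-up is expected. Without a record of admissions and deaths, such events could sit unnoticed among the patients counted as lost.

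**Working it through.** **Is the omission real?** It rests on reading the sections together, not on the confidentiality sentence, which only shows how narrow the risk section is.

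- Objectives and outcomes: none names hypoglycaemia, an adverse event, an admission or a death.
- Statistical methods: baseline description, univariable screening, and comparisons within and between groups; nothing on safety.
- Chronogram: no event recording.
- Risk sections: confidentiality, blood sampling and consent.
- Secondary judgment criteria announces two types of criteria and lists one. Nothing shown suggests that the missing type is safety.

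**Inputs for precision.** The protocol gives 60 evaluable patients per group and 75 recruited, with 20% loss. It gives no event rate, so every rate below is an assumption.

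**The plan's own figures.** 60/(1 − 0.20) = 75, which reproduces. The 60 does not reproduce exactly. With a common SD of 2.0, two-sided 5% and 80% power, n = (1.960 + 0.842)² × 2 × 2.0²/1² = 62.8, so 63 (power at 60 is 78.2%). With the two SDs as written, (1.960 + 0.842)² × (2.0² + 0.5²)/1² = 33.4, so 34. That is a separate matter. The present point uses 60 and 75 only as the numbers of patients who could be asked.

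**Zero events in an arm.** The one-sided 95% upper limit is 1 − 0.05^(1/n):

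- n = 60: 4.9%
- n = 75: 3.9%

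The upper end of a two-sided 95% exact interval is 1 − 0.025^(1/n): 6.0% at 60 and 4.8% at 75.

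**Comparing arms.** Two-sided 5% test of two proportions, normal approximation with pooled variance under the null:

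| Assumed rates | Power, 60 per arm | Power, 75 per arm |
|---|---|---|
| 5% vs 10% | 18% | 21% |
| 10% vs 20% | 33% | 40% |
| 20% vs 40% | 67% | 77% |

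If both arms had a 20% rate, the 95% half-width for the difference would be 1.96 × √(2 × 0.2 × 0.8/n), which is 14 points at 60 and 13 points at 75.

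Harm data in this trial would therefore describe what happened. They could not exclude a moderate excess. These figures count all patients in an arm; among insulin users alone, whose number the protocol does not give, precision would be poorer.

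**The case against.** The strongest reply is that the added data would settle little. They would be imprecise, recalled, and collected without blinding. That stands, and it limits what the fix can promise. It does not justify collecting nothing, since admissions and deaths depend less on recall and even a descriptive table would show a gross imbalance.

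Several stronger readings are tempting, and the documents do not carry them:

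- *Lay educators teach insulin management, so the hazard is direct.* The abstract lists such a topic, but Global method describes three cycles (cardiovascular risk, food, physical activity) and the text after it speaks of three meetings, with no insulin session. Nothing gives educators a role in changing doses; under Comparison group, prescribing belongs to the clinic consultation. The point does not need this premise, because use of medicines is among the practices to be changed.
- *The trial's goal is a 1-point fall.* One point is a sample-size assumption. The objective is to compare HbA1c improvement.
- *No harm data at all are collected.* Blood pressure, weight and fasting glucose can show unfavourable change, and visits include a clinical examination. None is defined or analysed as a safety outcome, and none captures hypoglycaemic episodes. The visit forms are not shown.
- *The investigators themselves suspect harm.* The caution under Ethical consideration concerns the programme's results in general.
- *Nothing could be recovered later.* Participants attend the diabetes units regularly, so severe events and deaths may be traceable there. Mild episodes are much less so.

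The protocol also says that a national ethics committee will monitor the study's commitments. Such oversight does not produce comparable event data by arm.

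**Conclusion.** The concern holds in limited form. No recording of hypoglycaemia, admissions, deaths or other adverse events is described for either arm, so a fall in HbA1c could not be set beside planned harm data when use in 22 units is decided. The primary comparison and the stated sample size are untouched.

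A reader might infer that recording harms would let the trial deliver a firm benefit-risk conclusion, or that without it a harmful programme would be reported as a success. Neither is supported. At 60 to 75 per arm the data would be descriptive, and nothing in the protocol shows how the result would be reported.

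The conclusion assumes that the visit forms, which are not shown, do not already carry such questions. The power figures rest on assumed event rates. The change is worth making, but the HbA1c result does not depend on it.

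**What to change.** At T3, T6 and T12, ask the same questions in the same words in both arms: the number of hypoglycaemic episodes since the last visit; how many needed another person's help or hospital care; and any other hospital admission. Record deaths, and follow up missed visits in the same way in both arms so that a death or admission is not filed as simple loss.

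Add these items to Secondary judgment criteria as safety outcomes. In the statistical methods, provide one table by arm giving the number of events and of patients affected, with exact confidence intervals for the proportions. State that the table is descriptive, that zero events in 60 to 75 patients leaves a one-sided 95% upper limit of 4.9% to 3.9%, and that recall in an open trial is a limit. State whether an insulin session is part of the programme, since the abstract and the detailed method differ.

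The cost is a few questions at visits that already take place, and one table. Sample size and visit schedule stay as they are.
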